## **5.2 DATA COLLECTION METHODS**

Hospital data collected by the hospital will be recorded on electronic Case Report Forms (eCRFs) designed specifically for this study in the data capture system. Source data will be documented in medical records. Patient reported outcomes (HADS and HRUQ) will be captured using versions of the questionnaires either sent directly from the database, completed over the phone with the research nurse or by postal questionnaire sent by the site. Given the short available time window between the post-operative clinic and the RS being received, questionnaires should be sent within 3 days of the post-operative clinic appointment date of the initial surgery where possible. If no response has been received within one week  $\pm$  3 days of the questionnaire being sent, the patient will be followed up by phone. Participants will be provided with a patient diary to record any health care interactions to aid in the HRUQ completion. Only data relevant to this study will be collected. Data collected in the CRFs will be pseudo anonymised and will not identify the participant. The Subject ID Number will link the CRFs to the source data during monitoring visits.

## Table of data collection

|                                                  |                                                                                                                                                                                                                                                                                                                                      |
|--------------------------------------------------|--------------------------------------------------------------------------------------------------------------------------------------------------------------------------------------------------------------------------------------------------------------------------------------------------------------------------------------|
| Baseline data                             | 
 
○ Consent
 
○ Demographics (year of birth, age, sex, ethnicity)
 
○ Histology / radiology / pathology reports on diagnostic investigations
 
○ Disease staging – TNM grading
 
○ HADS
 
○ Randomisation
 
                                         |
| Post consent                              | 
 
○ Oncotype DX® test date ordered on diagnostic biopsy (Intervention Arm only)
 
                                                                                                                                                                                                      |
| Surgery                                   | 
 
○ Results of surgery – histology, radiology, pathology reports
 
                                                                                                                                                                                                                     |
| Post-op results clinic                    | 
 
○ Oncotype DX® test date ordered (Standard Arm only) RS results delivered (intervention)
 
                                                                                                                                                                                           |
| One week after Post-op Clinic (± 4 days)  | 
 
○ HADS and HRUQ
 
                                                                                                                                                                                                                                                                    |
| ~2 weeks after Post-op clinic             | 
 
○ RS results delivered (Standard arm only)
 
                                                                                                                                                                                                                                         |
| Adjuvant treatment offer and prescription | 
 
○ Treatment type (specifics not required as not collecting treatment outcome data)
 
○ HADS and HRUQ
 
○ Number of clinician-participant interactions and participant touch points* (Patient approach to the offer and prescription of the first adjuvant treatment)
 
 |

\* Appendix A for definitions

## **6.0 SAMPLE COLLECTION**

There will be no study specific research samples collected. The diagnostic and surgical core biopsies documented in the study protocol are taken in routine clinical practice and will be collected and processed following standard local site protocols.

No additional samples will be retained for study purposes but consent will be sought for permission for further possible research testing on the biopsy tissue that is retained as part of standard clinical practice.

## **7.0 MONITORING**

A risk-based approach to monitoring will be adopted for PRE-DX. It is anticipated monitoring will be predominantly through a combination of central and remote monitoring. On-site monitoring is not expected unless an escalation is triggered as a result of the central or remote monitoring. A HHTU Study Monitoring Plan will be developed and agreed by the sponsor, CI and Trial Management Group (TMG).

A Data Monitoring Plan will be agreed by the sponsor, CI and statistician to provide detailed instructions and guidance relevant to database set up, data entry, validation, review, query generation and resolution, quality control processes involving data access and transfer of data to the sponsor at the end of the study and archiving. All the information obtained about participants in the course of the study is confidential and will be held in accordance with the General Data Protection Regulation (GDPR 2018).

Data will be monitored for quality and completeness by the HHTU. Missing data will be chased until it is received or confirmed as unavailable. HHTU will reserve the right to intermittently conduct CRF to database and source data verification to CRF exercises on a sample of participants. Source data verification may involve direct access to participant medical records at participating sites.

## 8.0 SAFETY REPORTING

As this study collects data on routine interventions, there are no study specific assessments that will affect study safety. Therefore, this study will not collect any adverse event or serious adverse event data. Should an Investigator have any concerns regarding participant safety as an outcome of their participation in the trial, they should contact the Trial Management Team ([[contact]](mailto:[contact])) and Chief Investigator ([[contact]](mailto:[contact])) to raise these concerns as soon as possible.

The TMG will be kept informed of diagnosis and treatment outcomes in regular study oversight meetings. Any trends that point towards patient harm will be identified and acted upon.

## 9.0 STUDY OVERSIGHT RESPONSIBILITIES

### 9.1 DAY-TO-DAY TRIAL MANAGEMENT

Day-to-day study management will be conducted by the HHTU study team who will work closely with the CI and sponsor. The HHTU study team will include a Trial Manager, Trial Coordinator, a Data Manager and a Trial Administrator with quality assurance and study oversight provided by members of the HHTU Senior Management Team. Study activities will be performed according to the relevant HHTU / Sponsor Standard Operating Procedures (SOPs).

### 9.2 TRIAL MANAGEMENT GROUP (TMG)

The TMG will comprise the CI, co-investigators, Sponsor representatives, HHTU personnel and lay representatives. The TMG will meet regularly until study recruitment begins and during the first three months of recruitment. Thereafter, the TMG will meet quarterly if progress is satisfactory and more frequently if not. Each meeting of the TMG will review achievement of milestones, rate of participant recruitment, data collection and safety issues. The need for an independent Trial Steering Committee was assessed by the Sponsor as part of the study risk assessment. As the study does not alter patient treatment, with no expected impact on patient safety, it was agreed that the TMG could conduct the oversight role for the study. If implementation challenges are identified, solutions will be sought and changes put in place. All TMG discussions will be minuted, with actions detailed, and reviewed at the following meeting.

If the risk profile of the study changes during the course of the study the need for an independent TSC would be reviewed.

## **10.0 COST IMPACT ANALYSIS**

This component of work aims to evaluate health system cost impacts from any potential streamlining of the patient management pathway due to the availability of the RS® results from the core biopsy in the pre-operative setting.

The hypothesis is that the availability of RS results from the core biopsy in the pre-operative setting will reduce healthcare utilisation between diagnosis and the commencement of adjuvant treatment. To evaluate this, the study will collect data on: i) the number of health care provider-participant touch points throughout the follow-up, and ii) the conduct of repeat testing (including cases where there is failure of the Oncotype DX® assay on core biopsy specimen and re-testing proceeds using the surgical specimen. Furthermore, a Health Resource Utilisation questionnaire (HRUQ) will be developed and applied at various data collection time points throughout the study. This will aim to identify any further impacts on health care resource use, for example, relating to contacts with primary care providers.

The resource utilization will then be costed using appropriate sources, including NHS reference costs and national tariffs.

Difference in resource use between the two arms of the trial will be descriptively summarised. Difference in total costs will be examined by linear regression controlling for the same stratification factors and prognostic covariates as the statistical analyses.

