## 2.0 AIMS AND OBJECTIVES

This study aims to compare the standard patient pathway (control arm), where the Oncotype DX® test is requested on the post-operative specimen with requesting the test on the pre-operative diagnostic core biopsy (intervention arm). The initial planned analyses will add to the evidence base of the patient management pathway of performing the Oncotype DX® test on the pre-operative diagnostic biopsy.

**Aim:** To assess the impact on patient management by the availability of the RS® results from the core biopsy in the pre-operative setting.

**Primary hypothesis:** The availability of the RS® results from the core biopsy in the pre-operative setting streamlines the patient management pathway

**Secondary hypothesis:** The availability of the RS® results from the core biopsy in the pre-operative setting reduces healthcare utilisation, improves patient experience and decreases the time to the offering of adjuvant cancer therapy.

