## **11.0 STATISTICAL ANALYSIS PLAN**

### **11.1 SAMPLE SIZE:**

A single retrospective cohort study in the UK demonstrated that the earlier availability of the RS results, when ordered from the post op MDT, reduced the average number of post-operative clinical appointments by 1 visit [5]. We hypothesise that the number of participant-clinician touch points in the control group is 6 visits per patient and our intervention is likely to reduce it to 5 visits per patient. With 2:1 recruitment ratio between intervention and control group and 20% dropout rate, a sample size of 330 in total is required (220 in intervention arm and 110 in control arm). This sample size was calculated by the sample size and power calculation software, nQuery [6], for comparison of numbers of touch points between intervention and standard arm using a Negative Binomial model, at 5% significance level and 90% power– see Appendix B for the screenshot of sample size calculation.

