### **11.2 STATISTICAL ANALYSIS:**

The reporting guideline of CONSORT 2010 statement [7] will be followed for analysis and reporting of this study. All statistical tests and confidence intervals will be two-sided.

Ninety-five percent confidence intervals will be presented with the significance of p value at 5% significance level. Analyses will be conducted on an intention-to-treat basis (all participants who are randomized are included in the statistical analysis, including those who fail to receive an RS result from either the diagnostic core biopsy or excision specimen) and follow a pre-specified statistical analysis plan. Baseline patient characteristics will be tabulated through descriptive statistics. For the primary outcome, comparison of the numbers of participant-clinician touch points will be undertaken using a Negative Binomial model, adjusting for stratification factors and other prognostic baseline covariates. Rate of alteration in treatment pathway and rate of failure of obtaining an RS result on diagnostic core biopsy specimen in the intervention arm will be summarised and a per-protocol analysis will be conducted as secondary analysis, excluding those with alteration in treatment pathway or failure to obtain RS result. Comparison of time between diagnosis and adjuvant treatment will be assessed via Cox regression controlling for the same stratification factors and prognostic covariates. HADS score at baseline, the post-operative result clinic and commencement of adjuvant treatment will be examined by linear regression controlling for the same stratification factors and prognostic covariates. Correlation of preoperative staging with postoperative pathological staging will be calculated.

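### Touchpoints and costs stop being counted at each participant's own adjuvant offer and prescription, so a lower count shows fewer contacts to reach the offer, not a net saving in healthcare use

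*Protocol*

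**What the plan says.** **Where counting stops.** Section 3.2 ends the primary count at the offer and prescription of the first adjuvant treatment. The Table of data collection in section 5.2 gives the span as "Patient approach to the offer and prescription of the first adjuvant treatment". Appendix A states the same stopping rule above both of its columns, the primary-outcome contacts and the wider health-economic contacts. Section 5.1 stops at the offer. The resource-use questionnaire (HRUQ) is completed after the post-operative clinic and after the offer, and only once if the two fall on the same date. No later collection of contacts is described.

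**What is expected to move.** The secondary hypothesis in section 2.0 is that the intervention "reduces healthcare utilisation, improves patient experience and decreases the time to the offering of adjuvant cancer therapy". Section 3.3 makes time to offer and prescription a secondary outcome. In the Table of data collection, the intervention arm gets the RS at the post-operative results clinic. The entry for about two weeks after that clinic reads "RS results delivered (Standard arm only".

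**What is counted.** Appendix A counts oncology, surgical, radiology and other breast-care outpatient contacts, whether or not they depend on the RS.

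**What is to be concluded.** Section 10.0 states that the intervention "will reduce healthcare utilisation between diagnosis and the commencement of adjuvant treatment", costs the touchpoints over a follow-up that it does not define, and compares total costs by linear regression. Section 1.0 expects unnecessary outpatient attendances to be avoided.

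**The concern.** The counting window ends at a post-randomisation event whose timing is itself a hypothesised effect of the intervention. Observation is therefore expected to be shorter in the intervention arm. Take a surgical nursing visit that falls on the same day after surgery in two participants. It is counted in the standard-arm participant who is still waiting for the RS, and not counted in the intervention participant who already has a prescription. Both used the same care.

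This does not harm the primary hypothesis: the number of contacts needed to reach an adjuvant offer is a fair measure of a streamlined pathway. The difficulty lies with the statements that go further, namely the utilisation hypothesis in section 2.0, which has no time window, the avoided attendances of section 1.0 and the health-system cost impact of section 10.0. Visits that were not collected cannot be recovered at the analysis stage.

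The windows also disagree. The cost hypothesis runs to commencement of adjuvant treatment, and section 3.0 runs the primary outcome to its start, but described touchpoint collection ends at offer and prescription. Contacts between prescription and start, where displaced visits could fall, belong to the cost hypothesis and have no described collection.

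**Working it through.** **Inputs from the protocol.** Section 11.1 supposes that "the number of participant-clinician touch points in the control group is 6 visits per patient" and that "our intervention is likely to reduce it to 5 visits per patient", "at 5% significance level and 90% power", with 2:1 allocation and 20% dropout. Section 11.2: "All statistical tests and confidence intervals will be two-sided". Appendix B: dispersion 0, with 88 and 176 evaluable.

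**Input not in the protocol.** d, the mean number of visits per intervention participant that move past the offer without being saved. Assumed range: 0 to 1.

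**Step 1: the plan's own figure.** With dispersion 0, control mean m0 = 6, intervention mean m1 = 5 and ratio k = 2:

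- Alternative variance V1 = 1/6 + 1/(2×5) = 0.2667
- Pooled null variance V0 = (1+k)²/[k(m0 + k·m1)] = 9/(2×16) = 0.28125
- n(control) = (1.960√V0 + 1.2816√V1)² / ln(5/6)² = 2.894/0.03324 = 87.07, so 88 and 176
- Dropout: 88/0.8 = 110 and 176/0.8 = 220, total 330

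The sample size reproduces exactly, with 90.3% power at 88 v 176. There is no arithmetic error; the point is what gets counted.

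**Step 2: displacement with no visit saved.** Let both arms have 6 visits over a common period, and let the intervention arm show 6 − d inside its window. The chance of a significant reduction is Φ{[ln(6/(6−d))·√88 − 1.960√V0]/√V1}, with m1 = 6 − d.

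Example, d = 0.5: V1 = 1/6 + 1/11 = 0.2576; V0 = 9/(2×17) = 0.2647; ln(6/5.5) = 0.0870. This gives (0.816 − 1.008)/0.5075 = −0.379, and Φ = 35%.

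The simulation drew 40,000 Poisson trials per row and applied a Wald test on the log rate ratio.

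| d | In-window rate ratio | Chance, formula | Chance, simulation | Chance over a common window, simulation |
|---|---|---|---|---|
| 0 | 1.00 | 2.5% | 2.4% | 2.4% |
| 0.25 | 0.96 | 12% | 12% | 2.4% |
| 0.5 | 0.92 | 35% | 37% | 2.7% |
| 0.75 | 0.88 | 67% | 69% | 2.6% |
| 1.0 | 0.83 | 90% | 91% | 2.6% |

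Taken together, the in-window chances are about 12%, 36%, 68% and 90%. One displaced visit looks the same in these data as one saved visit.

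**Step 3: part displaced, part saved.** Suppose the in-window difference is the planned 1 visit. If 25%, 50% or 75% of it is displacement, the true saving is 0.75, 0.5 or 0.25 visits. Power over a common window (control mean still 6) is then 67%, 35% or 12%, against 90% in-window.

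**The case against.** Several objections stand.

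- **The hypothesis in section 10.0 has a window.** Contacts on the way to adjuvant treatment are a legitimate quantity. A reader might infer that the utilisation hypothesis cannot be answered at all. That goes too far: the question limited to the window can be answered for the period actually collected, and only the step to a net saving fails.
- **Displacement is possible, not shown.** A reader might spread six visits evenly over an assumed 50 to 90 days and get 14 × 6/90 = 0.9 to 14 × 6/50 = 1.7 visits in a 14-day wait, the whole planned effect or more. The documents support neither the duration nor the even spacing. The two weeks concern RS delivery, not the difference in offer date. Even spacing also counts as displaced the RS-result contact that the intervention may truly remove. Zero displacement remains possible.
- **The percentages describe the primary count, not the cost regression.** No figure for bias in cost can be derived from the documents.
- **Some extra intervention contacts do count against it**: the additional clinic visit when a recommendation changes (section 3.1) and repeat testing (section 10.0). This does not make observation time equal.
- **A plain fixed window could reverse the bias**, because the arm prescribed sooner may also start sooner and accrue treatment attendances inside it. The fix has to exclude these.

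It can also be said that the undefined follow-up in section 10.0 leaves the cost window open. Appendix A answers most of this, since its stopping rule covers the health-economic contacts too, and no later collection is described.

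**Conclusion.** The concern holds in a limited form. The planned data cannot tell a contact moved past the offer from a contact saved. A lower in-window count or cost can be reported as fewer contacts, or less cost, up to the adjuvant offer and prescription. It cannot carry the general utilisation claim of section 2.0, the avoided attendances of section 1.0 or a net saving under section 10.0. Section 10.0 also states a window that ends later than the described touchpoint collection.

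The size is unknown. The illustration of about 12%, 36%, 68% or 90% assumes no visit truly saved, Poisson counts with control mean 6, 88 v 176 evaluable, and displacement of 0.25, 0.5, 0.75 or 1.0 visits. It shows that half a displaced visit would matter against a planned effect of one visit, not that this will happen. The primary outcome and the sample size are not called into question by this point.

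**What to change.** 1. Keep the count to offer and prescription as the primary measure of streamlining.
2. Give section 10.0 one window end that matches what is collected, and make sections 3.0, 5.1 and 10.0 agree with section 3.2 and Appendix A. Moving the end to treatment start would need further collection, and would still close at each participant's own event.
3. Limit utilisation and cost conclusions to the stated window.
4. For any claim of net saving, add a supplementary comparison of hospital-recorded contacts in both arms up to one common time from randomisation, excluding attendances for delivering or monitoring adjuvant treatment. Report it beside the in-window result, as an estimate with its confidence interval, since Step 3 shows that it may have little power.

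**Cost.** A protocol and eCRF amendment, and a few more weeks of record extraction for participants with an early offer. No extra visit or questionnaire is needed. GP contacts stay limited to the HRUQ window, so the supplementary comparison covers hospital contacts only.

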### **3.2 PRIMARY OUTCOME**

- Number of participant touch points defined as a participant-clinician interaction (outpatient appointment or equivalent) between the treating team and the participant from the participant diagnosis (defined as the date of attendance at diagnostic clinic) to the offer and prescription\* of the first adjuvant cancer treatment (see Appendix A for definitions). In the event of the participant declining further treatment the date of offer should be used.

For those participants receiving bridging therapy, the date of the confirmation of adjuvant systemic therapy (endocrine or chemotherapy) will be used.

\*Defined as the date prescription is documented as being issued in the clinic appointment or letter sent to GP to request prescription or treatment entered into Chemocare or equivalent.

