## APPENDIX A - DEFINITIONS OF PARTICIPANT-CLINICIAN INTERACTIONS AND PARTICIPANT TOUCH POINTS

The list provides examples of clinical interactions (participant-clinician) and participant touch points.

Participant approach is touchpoint zero, all other touchpoints from that point onwards until **the first** adjuvant treatment **is offered and prescribed** are counted.

| Hospital reported Participant-Clinician Interactions – primary outcome | Participant and hospital reported healthcare touchpoints – health economic outcomes |
|------------------------------------------------------------------------|-------------------------------------------------------------------------------------|
| Oncology Clinician outpatient visits or equivalent                     | As Hospital reported plus:                                                          |
| Oncology nursing outpatient visits or equivalent                       |                                                                                     |
| Surgical clinician outpatient visits or equivalent                     | GP visits                                                                           |
| Surgical nursing outpatient or equivalent                              | GP Practice Nurse visits (home)                                                     |
| Radiology clinician outpatient visits or equivalent                    | GP Practice Nurse visits (surgery)                                                  |
| Radiology nursing outpatient visits or equivalent                      | A&E visits related to breast care                                                   |
| Other breast care related secondary care visits or equivalent          |                                                                                     |

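### The reduced-utilisation hypothesis is tested only in part: contacts beyond the hospital count, and repeat testing, are described without a between-arm estimate

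*Protocol*

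**What the plan says.** Section 2.0 gives a secondary hypothesis with three limbs, namely that having the result "in the pre-operative setting reduces healthcare utilisation, improves patient experience and decreases the time to the offering of adjuvant cancer therapy". Section 10.0 repeats the first limb: the intervention "will reduce healthcare utilisation between diagnosis and the commencement of adjuvant treatment".

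To evaluate it, section 10.0 names "i) the number of health care provider-participant touch points throughout the follow-up" and "ii) the conduct of repeat testing", and adds the HRUQ to pick up further use such as primary-care contacts. On analysis it says "Difference in resource use between the two arms of the trial will be descriptively summarised". Total cost alone is given a model, a linear regression adjusted for the stratification factors and prognostic covariates.

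Appendix A has two columns. The left lists hospital-reported interactions and is the primary outcome. The right is headed "Participant and hospital reported healthcare touchpoints – health economic outcomes" and consists of the left column plus GP visits, practice-nurse visits and A&E visits related to breast care. Section 11.2 compares the left-column count between arms with an adjusted Negative Binomial model and a 95% confidence interval. It names no model for the right-column count.

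**The concern.** The protocol makes reduced utilisation a named, directional hypothesis and then chooses a descriptive method for the count that would measure it most broadly. The other two limbs of the same hypothesis get adjusted models in section 11.2: Cox regression for time and linear regression for HADS.

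At stake is how a positive primary result can be read. If hospital contacts fall by about one per patient, a reader will ask whether total contacts also fell. The plan would answer with a table of means by arm and a cost difference. Neither gives the net change in contacts with a measure of uncertainty.

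**Working it through.** **1. What each planned analysis covers**

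| Component of utilisation | Primary model (11.2) | Total-cost model (10.0) | Own between-arm estimate named? |
|---|---|---|---|
| Hospital contacts | yes | yes, priced | yes |
| GP, practice-nurse, breast-related A&E contacts | no | yes, priced | no |
| Hospital plus these contacts (Appendix A, right column) | hospital part only | only as priced | no |
| Repeat testing | no | yes, priced | no |

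The windows also differ. The primary count ends when the first adjuvant treatment is offered and prescribed (section 3.2, Appendix A). The section 10.0 hypothesis runs to the commencement of adjuvant treatment.

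**2. The plan's own size, for the hospital count**

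Inputs (section 11.1, Appendix B): 6 against 5 visits, two-sided 5%, 90% power, 2:1 allocation, dispersion 0, 20% dropout.

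- Variance under the null (pooled rate): V0 = (1+2)² / [2 × (6 + 2×5)] = 9/32 = 0.28125.
- Variance under the alternative: V1 = 1/6 + 1/(2×5) = 0.26667.
- Control n = (1.960 × √0.28125 + 1.2816 × √0.26667)² / ln(5/6)² = 87.07, rounded up to 88. Intervention n = 176.
- Dropout: 88/0.8 = 110 and 176/0.8 = 220, total 330.

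This reproduces the stated figures. The trial is sized for inference on the hospital part of utilisation.

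**3. What a model of the wider count could deliver**

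The documents give no rates for the wider count. As an illustration, assume the extra contacts add 2 or 4 per patient in both arms and the saving stays at 1, giving 8 against 7 or 10 against 9. With 88 and 176 evaluable:

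- V = 1/r0 + 1/(2 × r1) + 1.5 × k, where r0 and r1 are the control and intervention rates and k is the dispersion.
- Power = Φ(|ln(r1/r0)| × √(88/V) − 1.96).
- 95% interval if the assumed ratio is observed = exp(ln(r1/r0) ± 1.96 × √(V/88)).

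| Assumed rates | k | V | Power | Ratio (95% interval) |
|---|---|---|---|---|
| 8 vs 7 | 0 | 0.1964 | 81% | 0.875 (0.80 to 0.96) |
| 8 vs 7 | 0.1 | 0.3464 | 57% | 0.875 (0.77 to 0.99) |
| 10 vs 9 | 0 | 0.1556 | 71% | 0.90 (0.83 to 0.98) |
| 10 vs 9 | 0.1 | 0.3056 | 43% | 0.90 (0.80 to 1.01) |

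These intervals would be informative, but power is below the planned 90%. The result is better reported as an estimate than relied on as a test.

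**4. Can total cost stand in for contacts?**

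Total cost weights each item by price and includes repeat assays. The documents give no unit prices and no expected failure rate. If an assay costs an assumed 5, 10 or 20 times a visit, the saving from one visit is cancelled by 1/5 = 0.20, 1/10 = 0.10 or 1/20 = 0.05 extra assays per intervention patient, net of any in the control arm. Cost and contacts could therefore move differently as a matter of arithmetic. The documents cannot show whether they will.

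**The case against.** The strongest reply is that utilisation is already tested: touch points are the first measure section 10.0 names, and the trial is sized on them. That stands for the hospital part. A reader might infer that the utilisation hypothesis receives no inferential analysis at all; the documents do not support that.

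Second, repeat testing is itself part of utilisation in section 10.0, so total cost is the one modelled quantity that combines everything. This also stands in part. It rules out treating repeat assays as mere contamination of the cost result, and it means a contact count alone would not cover the whole hypothesis. It does not make cost an estimate of contacts.

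Third, the cost comparison is the secondary outcome listed in section 3.3 and it is modelled. Describing resource items and modelling total cost is a common layout. This is why the point is minor.

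Fourth, an unseen analysis plan may add an interval. It may, but the protocol is not silent here: it fixes the method as descriptive.

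Two stronger readings are tempting. One is that cost will reverse a true fall in contacts; that rests on assumed prices and failure rates. The other is that work shifts to primary care, because one prescription route is a "letter sent to GP to request prescription". That letter only helps date the end of the primary count, in both arms alike, and is no evidence of a shift.

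Finally, the wider count is harder to build than the hospital one. It mixes hospital and participant reports. Section 5.1 drops the second questionnaire when both follow-up events fall on the same date, and section 3.1 stops collection after a change of pathway. The last also stops touch points, so it affects the primary outcome equally. These are real limits on the extra analysis, but not reasons to leave it out.

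**Conclusion.** The point holds in a limited form. The secondary hypothesis of reduced utilisation is tested for hospital contacts and approached through total cost. The wider Appendix A count and repeat testing are only described, and no planned model isolates the net change in contacts. This follows from sections 2.0, 10.0 and 11.2 and Appendix A without any assumption. The precision figures and cost break-evens above rest on assumed rates, dispersion and prices and serve only as illustration.

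The primary comparison and the sample size are unaffected. This is a cheap improvement, not a defect that threatens the trial's main conclusion.

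**What to change.** In section 10.0, replace the descriptive-only sentence with the following content:

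- Estimate the between-arm difference in total contacts in the right-hand column of Appendix A: hospital-reported contacts plus participant-reported GP, practice-nurse and breast-related A&E contacts, each counted once.
- Use the same adjusted count model as the primary outcome, over a stated window.
- Report the ratio and the mean difference with 95% confidence intervals, labelled as a supportive secondary estimate.
- Report repeat testing by arm alongside it, and keep the item-by-item breakdown descriptive.

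The minimum alternative is to say in sections 2.0 and 10.0 that utilisation beyond the primary outcome is exploratory and descriptive.

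The cost is one more secondary analysis on data already planned for collection, with no new visits. It needs a rule for overlap between hospital and participant reports, and its precision and completeness will depend on HRUQ return.
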